#### Secondary outcomes

*Muscle strength*: the manual muscle test (MMT) will be used to test the muscle strength of flexor and extensor in knee and hip.

*Range of Motion (ROM)*: the goniometer will be used to measure the active and passive flexion and extension ROM in hip, knee, and ankle joint.

*Alignment:* the Q angle will be measured via the X-ray.

*Joint space:* the joint space will be quantified by X-ray.

*Cytokines in serum:* TNF-*α*, interleukin-1β (IL-1β), interleukin-15 (IL-15), C1q/tumor necrosis factor-related protein-9 (CTRP9), and interleukin-29 (IL-29), CRP, hs-CRP, MMP-3, MMP-13, HA, NO, MDA, PGE-2.

*Cytokines in synovial fluid:* interleukin-34 (IL-34), interleukin-37 (IL-37), and interleukin-6 (IL-6).

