### Sample size

GPower 3.1 software (Heinrich-Heine-Universitat, Dusseldorf, Germany) was used to estimate the sample size. Wang et al. (36) 8-week traditional Chinese herbs hot compress (TCHHC) trial demonstrated a significant interaction on the total WOMAC score between the TCHHC combined with therapeutic exercise group and the therapeutic exercise alone group, yielding a partial eta-squared (
$\eta_{p}^{2}$
) of 0.148, corresponding to an effect size of *f* = 0.416 (36). A conservative approach was adopted for our sample size estimation, considering the comparison of two distinct treatment factors—ECHT and PEMF—and their combined application, alongside a reduced intervention duration of 4 weeks. Employing a 4 (group factor) × 3 (time factor) RM ANOVA framework, and assuming a small effect size (*f* = 0.15), a significance level (*α*) of 0.05, statistical power of 0.80, and accounting for a 15% attrition rate, the total sample size required was 124 participants, evenly distributed across the four groups, i.e., 31 in each group. The sample size is expanded by 10% compared to the original registration in the Chinese Clinical Trial Registry. This modification was necessitated by a post-initiation adjustment to the attrition rate assumption, which was revised upward to a more conservative 15% based on emerging data from the ongoing trial.

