### Statistical analysis

Data entry will be performed by two independent researchers so that the accuracy of the input data can be cross-checked. The Statistical Package for Social Sciences (SPSS) version 26 will be used to conduct the data analysis. Intention-to-treat analysis will be performed. The normality of the data will be checked using the Shapiro–Wilk test. To compare the baseline characteristics of the four groups, one-way ANOVA (or its nonparametric equivalent: Kruskal–Wallis test) or Chi-square tests will be used, depending on whether the criteria for parametric statistics are fulfilled. Those relevant variables that show important between-group differences will be entered as covariates for subsequent analysis. To compare the treatment effects of the 4 intervention approaches, multivariate 4 × 3 ANOVA or ANCOVA with repeated measures (mixed design; repeated factor: time; between-subject factor: group) will be used to determine the time effect and treatment × time interaction effect for each outcome variable of interest. The Greenhouse–Geisser correction will be applied if the assumption of sphericity is violated. If significant results are found, *post-hoc* multiple comparisons of group effects and contrast analyses of time effects will be performed. Bonferroni adjustment will be performed in *post-hoc* analysis to account for the increased risk of Type I errors associated with multiple comparisons. If the criteria for parametric statistics are not fulfilled, the Mann–Whitney test and Wilcoxon test will be used.

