## Discussion

This trial is poised to conduct a thorough comparative analysis of the impacts of ECHT, PEMF therapy, and their combined application on pain alleviation, functional improvement, and the modulation of blood inflammatory biomarkers in older adults with KOA. The study is meticulously designed to test the central hypothesis that a synergistic approach, integrating both ECHT and PEMF therapies, will induce more pronounced alterations in blood inflammatory biomarkers. This, in turn, is hypothesized to result in superior improvements in pain and functional capabilities compared to either intervention employed in isolation.

The study’s objectives are twofold: (1) to rigorously evaluate whether the integration of ECHT and PEMF therapy can achieve more significant modulation of inflammatory biomarkers, which are pivotal in the pathophysiology of KOA. (2) To determine if this combined therapeutic strategy leads to enhanced clinical outcomes in terms of pain reduction and functional enhancement in the elderly population suffering from KOA.

The implications of this trial are profound, as it seeks to provide evidence-based guidance for intervention strategies tailored to the unique needs of older adults with KOA. By elucidating the potential synergistic effects of ECHT and PEMF therapy on inflammatory pathways, the study aims to contribute to a deeper understanding of the mechanisms underlying pain relief and functional improvement in KOA. This knowledge is critical for advancing the development of personalized treatment plans that are both effective and safe for this vulnerable patient demographic.

Ultimately, the findings of this study will not only inform clinical practice by offering data-driven recommendations but also enrich the scientific discourse on the complex interplay between inflammation, pain, and function in KOA. The pursuit of these insights is essential for advancing the frontiers of OA management and enhancing the quality of life for older adults affected by this debilitating condition.

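### Skewed serum concentrations get no log-scale step: the plan goes from the 4 × 3 ANOVA straight to rank tests that cannot answer its own group-by-time question

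*Protocol article*

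**What the plan says.** The Statistical analysis section checks normality with the Shapiro–Wilk test. It then applies a 4 × 3 repeated-measures ANOVA, or ANCOVA where baseline differences call for covariates, which "will be used to determine the time effect and treatment × time interaction effect for each outcome variable of interest". The only alternative is stated in the section's last sentence: "If the criteria for parametric statistics are not fulfilled, the Mann–Whitney test and Wilcoxon test will be used". No log or other transformation is mentioned anywhere in the article.

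The section on secondary outcomes lists 13 serum markers: TNF-α, IL-1β, IL-15, CTRP9, IL-29, and then "CRP, hs-CRP, MMP-3, MMP-13, HA, NO, MDA, PGE-2". In the Discussion the central hypothesis is that combining the two therapies "will induce more pronounced alterations in blood inflammatory biomarkers", and modulation of inflammatory biomarkers is the first of the two objectives. The sample size was set on the total WOMAC score, not on a marker. No SD, coefficient of variation, correlation or expected effect is given for any marker.

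**The concern.** Serum concentrations cannot be negative, usually have a long right tail, and often change in proportion to their level. On the measured scale a few participants with high values can dominate the error term. The usual remedy is to analyse logarithms, which keeps the planned model. This plan has no such step: once the parametric criteria fail, it moves directly to rank tests.

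That move changes the question. Mann–Whitney compares two groups and Wilcoxon compares two occasions. Neither tests the four-group treatment × time interaction that the section sets as its target. Used directly, neither carries the promised covariates or gives an effect ratio. The model that was planned would therefore often be dropped for the very outcomes on which the first objective rests. Depending on the branch taken and what is ranked, power may be lost as well.

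**Working it through.** **1. Sample size, and the number of completers.** The inputs from the Sample size section are f = 0.15, 4 groups, 3 times, "a significance level (*α*) of 0.05, statistical power of 0.80, and accounting for a 15% attrition rate". The article gives neither the correlation between visits nor the sphericity factor, so 0.5 and 1 are assumed.

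- Noncentrality = N × f² × m / (1 − ρ) = 105 × 0.0225 × 3 / 0.5 = 14.175, with df 6 and (105 − 4) × 2 = 202.
- N = 105 is the smallest total that reaches 0.80; power at N = 104 is 0.799.
- 105 / 0.85 = 123.5, rounded up to 124, or 31 per arm. The plan's figure is reproduced.
- Completers per arm: 31 × 0.85 = 26.35, taken as 26.

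**2. Assumptions for the markers (none is in the documents).** Lognormal values; log SD 0.6, 0.8 or 1.0, so CV = √(exp(SD²) − 1) = 66% to 131%; correlation between visits on the log scale 0.5 or 0.7; arm ratios 1 / 0.8 / 0.8 / 0.6 at both post-baseline visits; α = 0.05.

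**3. How often the normality check fails.** Shapiro–Wilk rejects in 85% to 99% of samples of 31 over log SD 0.6 to 1.0. With milder skew, and two arms of 26, it rejects in at least one arm in 55% of trials at log SD 0.3, 89% at 0.5 and 98% at 0.7.

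**4. Power by branch (simulation, 2,000 to 4,000 trials per row).** The interaction columns use all four arms. The rank column compares combination with control by Mann–Whitney on raw change, set against a t-test on log change.

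| log SD | ρ | Interaction, raw | Interaction, log | Loss | Mann–Whitney, raw change | t-test, log change | Loss |
|---|---|---|---|---|---|---|---|
| 0.6 | 0.5 | 50% | 76% | 26 | 68% | 86% | 18 |
| 0.6 | 0.7 | 70% | 95% | 25 | 88% | 98% | 10 |
| 0.8 | 0.5 | 23% | 46% | 23 | 44% | 62% | 18 |
| 0.8 | 0.7 | 38% | 72% | 34 | 64% | 83% | 19 |
| 1.0 | 0.5 | 13% | 31% | 18 | 32% | 45% | 13 |
| 1.0 | 0.7 | 21% | 51% | 30 | 44% | 64% | 20 |

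A repeat run gave interaction power of 12% to 68% on raw values against 31% to 94% on logs. The plan does not say whether change scores or post-treatment values would be ranked. Mann–Whitney on post-treatment values is about equal to the log-change t-test at ρ = 0.5 and 13 to 25 points lower at ρ = 0.7. Type I error stays at 4% to 6%.

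**5. Sensitivity to milder skew, following the plan's own normality check.** Two arms, ρ = 0.5, effect sized for about 80% power on the log scale.

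| log SD | Net loss if change is ranked | Net loss if post values are ranked |
|---|---|---|
| 0.3 | 9 | 5 |
| 0.5 | 14 | 4 |
| 0.7 | 17 | 1 |

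**The case against.** **The raw scale is inferred.** The article never says that values will be analysed untransformed, it condenses a longer protocol, and an unseen analysis plan could add a transformation. This is a fair limit on the wording. But the article does state what happens when the parametric criteria fail, and that is rank tests. An analysis plan faithful to it would not reach the log scale.

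**The model favours logs.** Lognormal data with proportional effects is the case in which log analysis does best, so the direction of the power result is built in. Nothing in the documents shows that each of the 13 markers behaves this way. This stands: the power figures are conditional. The mismatch between the rank tests and the interaction question does not depend on them.

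**One headline loss for the whole plan.** A reader might infer that the biomarker comparisons simply lose 10 to 34 points. The documents do not support that. The upper end belongs to the raw ANOVA, a branch that the normality check would seldom leave in use at such skewness. On the rank branch the loss can be close to nothing: Mann–Whitney on post-treatment values is unchanged by taking logs.

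**Synergy on the wrong scale.** A reader might also infer that the plan would misread synergy, because two independent 20% reductions give 0.8 × 0.8 = 0.64, against 1 − 0.2 − 0.2 = 0.60 under raw additivity. This does not hold. No ECHT × PEMF interaction contrast is planned. The hypothesis is superiority over each single therapy, and 0.64 lies below 0.80 on either scale. Additive or multiplicative is a choice that the article leaves open. Even if a raw-scale 2 × 2 test were run with purely multiplicative effects, it would reject in about 5% to 12% of trials against a nominal 5%.

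**Importance.** The markers are secondary, VAS pain and WOMAC are primary, and type I error is not harmed. All true. This is a matter of efficiency and of answering the stated question, not of validity.

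**Conclusion.** The point holds in a limited form. For right-skewed concentrations the stated rule would usually replace the planned 4 × 3 model with two-sample and paired rank tests that cannot test the four-group interaction, adjust for covariates or give an effect ratio. That follows from the plan's wording and needs only the usual skewness of such assays.

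The power cost is conditional on lognormal markers with proportional effects, log SD 0.6 to 1.0, correlation 0.5 to 0.7 and 26 completers per arm. It is about 18 to 34 points on the raw ANOVA branch. On the rank branch it is about 10 to 20 points with change scores and about 0 to 25 with post-treatment values. These are alternative branches and should not be merged into one range. The primary outcomes are untouched.

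**What to change.** In the Statistical analysis section, state that:

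- each serum concentration is natural-log transformed at all three visits before analysis;
- the planned 4 × 3 model and the arm contrasts are run on the log values;
- results are given as ratios of geometric means with 95% CI;
- one fixed substitution rule for values below the assay limit applies in all arms;
- rank tests are a sensitivity analysis, and a normality test on raw concentrations does not choose the method.

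This takes a few sentences and no new data or participants. The cost is that results read as ratios rather than differences, and that the assay-limit rule must be fixed in advance. It should be settled before any unblinded analysis.

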**Methods and analysis:**

This randomized controlled trial (RCT) aims to enroll 124 older adults with KOA and will randomly allocate them across four treatment groups: (1) exercise with health education, (2) exercise with ECHT, (3) exercise with PEMF therapy, and (4) exercise with a combination of ECHT and PEMF. Each intervention will be administered five times per week for 4 weeks. The primary endpoints are pain and functional capacity, while secondary measures encompass lower limb range of motion, alignment, joint space, and serum cytokine levels. Assessments will be conducted at baseline, post-intervention, and at the 4-week follow-up.

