#### Primary outcomes

*Pain:* overall average pain severity in the past week will be measured via an 11-point visual analog scale (VAS) with terminal descriptors of “no pain” (score 0) and “worst pain possible” (score 10) (30). The minimum clinically important difference of NPRS was shown to be 1.8 (31, 32).

*Overall function:* the Western Ontario and McMaster Universities (WOMAC) Osteoarthritis Index (Likert version 3.1) will be used to measure the overall function in the past week (33). A total of 24 questions are divided in three categories assessing pain, stiffness and physical function, with Likert response options ranging from 0 (none), 1 (mild), 2 (moderate), 3 (severe), to 4 (very severe). A higher score indicates more intense pain, stiffness and physical dysfunction. Though WOMAC is a self-report, disease-specific instrument, excellent test–retest reliability (ICC = 0.83) and convergent validity (Pearson’s r = 0.77) have been demonstrated (34, 35).

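### VAS pain and WOMAC are both primary with no rule linking them; if either alone counts as success, the family-wise error of the two interaction tests is about 7.3% to 9.75%, not 5%

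*Protocol article*

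**What the plan says.** The Abstract states: "The primary endpoints are pain and functional capacity". The Primary outcomes section gives each its instrument. For pain, "overall average pain severity in the past week will be measured via an 11-point visual analog scale (VAS"). For function, the WOMAC index "will be used to measure the overall function in the past week"; its 24 items include a pain category, so the two outcomes overlap in content.

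The Sample size section describes one 4 × 3 repeated-measures ANOVA, "assuming a small effect size (*f* = 0.15"), with "a significance level (*α*) of 0.05, statistical power of 0.80" and 15% attrition, and arrives at 124 participants. The only outcome it mentions is the WOMAC total score, in the earlier trial it cites.

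The Statistical analysis section runs the 4 × 3 model to determine the time effect and the "treatment × time interaction effect for each outcome variable of interest". If a result is significant, post-hoc comparisons follow with a Bonferroni adjustment, "to account for the increased risk of Type I errors associated with multiple comparisons". Nothing is said about error across the two primary outcomes.

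**The concern.** A single alpha of 0.05 is stated, but two primary tests can each use all of it. The planned Bonferroni step works within one outcome, on group and time comparisons, and only after that outcome's overall test has passed. It does not limit the chance that at least one of the two overall tests is falsely significant.

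Without a stated rule, the authors could report a positive trial on VAS alone, on WOMAC alone, or on both, and choose the description after seeing the data. The first two would be made at an error rate above the stated 5%. The choice of rule also bears on the sample size, because 124 was derived for one test at the full 0.05.

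**Working it through.** **Inputs.** From the Sample size section: k = 4 groups, m = 3 times, f = 0.15, alpha 0.05, power 0.80, attrition 15%, total 124. From the Abstract and Primary outcomes: 2 primary outcomes. Assumed, because the article does not give them: correlation between time points ρ = 0.5, sphericity ε = 1, and the correlation r between VAS and WOMAC, varied from 0 to 0.9.

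**Step 1. Reproduce 124.** For the group × time interaction:
- λ = f²·N·m/(1 − ρ), df1 = (k − 1)(m − 1) = 6, df2 = (N − 4)·2.
- At N = 105: λ = 0.0225 × 105 × 3 / 0.5 = 14.175, df2 = 202, power = 0.804. At N = 104, power is 0.799, so 105 is the smallest N.
- 105 / 0.85 = 123.5, rounded up to 124 (31 per group).

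This matches exactly. The sample size is therefore that of one interaction test at 0.05.

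**Step 2. Error across two tests at 0.05.** If independent: 1 − 0.95² = 0.0975.

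For correlated outcomes, both interaction F tests were simulated under no effect (60,000 runs per r, 26 per group, 6 and 200 df; simulation error about ±0.2 percentage points):

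| r between outcomes | At least one significant at 0.05 | At least one significant at 0.025 each |
|---|---|---|
| 0 | 9.8% (exact 9.75%) | 4.8% |
| 0.3 | 9.5% | 4.8% |
| 0.5 | 9.0% | 4.5% |
| 0.7 | 8.6% | 4.3% |
| 0.8 | 8.0% | 4.1% |
| 0.9 | 7.3% | 3.9% |

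Each single test held its level (4.9% to 5.1%).

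**Step 3. If both had to succeed.** Under no effect on either outcome, P(both) = 0.05 + 0.05 − P(at least one). This runs from 0.10 − 0.0975 = 0.25% at r = 0 to 0.10 − 0.073 = 2.7% at r = 0.9. There is no inflation, but power for both is below the power for one: 0.80² = 0.64 if the outcomes were independent, and higher with correlation.

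**Step 4. Price of a plain split.** At alpha 0.025 and N = 105, λ stays at 14.175 and power falls from 0.804 to 0.716. Regaining 0.80 takes 122 evaluable participants; 122 / 0.85 = 143.5, so 144 enrolled (36 per group).

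**The case against.** **Silence in a condensed article.** A rule across primary outcomes is often left to the full protocol or the SAP. That would settle the matter if the article left multiplicity open. It does not: it states a multiplicity rule, gives Type I error as the reason, and places it only in the post-hoc step. As published, the rule is badly placed.

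**Both may be intended.** The hypotheses in the Introduction and Discussion speak of pain and function together. A both-must-succeed rule would remove the inflation (Step 3), but neither section makes joint significance a condition of success. What stands is that the inflated figure is conditional on either outcome being enough.

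**The word multivariate.** It could suggest a joint test across outcomes. The same sentence goes on to determine effects separately for each outcome, and no joint test is made a condition for the individual ones.

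**Omnibus tests are not treatment claims.** This is the strongest point, and it largely stands. Group claims must pass the interaction test and then Bonferroni. Simulating that sequence with no effect anywhere (20,000 runs per r; six pairs, change from baseline at either later visit; assumed details) gives a false pairwise claim on either outcome in 7.0%, 6.6%, 5.7% and 5.4% of trials at r = 0, 0.6, 0.8 and 0.9. A Bonferroni that also counts both visits brings it to about 5% or below. Error can be higher when some groups differ and others do not.

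**Overlap lowers the figure.** Because WOMAC contains pain items, a high correlation is plausible, which points to the lower part of the range. The article gives no value, so the whole range is shown.

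**Conclusion.** The point holds in a limited form. Two primary outcomes share one alpha of 0.05 with no rule between them. If a significant interaction on either counts as primary success, the family-wise error of the two omnibus tests is about 7.3% to 9.75% for outcome correlations from 0.9 to 0. This should be fixed, but it does not undermine the design.

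A reader might infer more than the article supports:
- *That the trial's type I error is about 9%.* This depends on either-outcome success and on a moderate correlation, neither of which is stated, and it counts omnibus tests rather than pairwise claims.
- *That the biomarker claim is close to a coin flip.* The Discussion does set out "to rigorously evaluate whether the integration of ECHT and PEMF therapy can achieve more significant modulation of inflammatory biomarkers" as an objective, and 1 − 0.95¹³ = 49% for 13 serum markers. But the markers are listed as secondary outcomes, where strict control is a preference, and 49% assumes independence although the list includes both CRP and hs-CRP.
- *That a single primary time point is needed.* The sample size was computed for an interaction over three times, and the gap between the two outcomes does not depend on it.
- *That the sample size rests on WOMAC alone.* The cited trial's WOMAC result was f = 0.416; the plan then adopts a generic f = 0.15 tied to neither outcome.

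**What to change.** Add one sentence to Statistical analysis, dated before outcome data are analysed, giving one success rule for the two primary outcomes. Either of these would do:

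1. **Holm** on the two interaction p-values: the smaller against 0.025 and, if significant, the larger against 0.05. Power for a given outcome at 105 completers then lies between 0.716 and 0.804.
2. **Fixed order**: for example WOMAC at 0.05, then VAS at 0.05 only if WOMAC is significant. WOMAC is a natural first choice as the outcome of the trial cited for the sample size, though f = 0.15 does not compel it. WOMAC loses no power; the price is that VAS cannot be claimed if WOMAC fails.

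If the authors intend that both must succeed, saying so also closes the gap, but power for the joint claim should then be stated, since it is below 0.80. A plain 0.025 split is valid but the least attractive: power per outcome drops to about 0.72 (with ρ = 0.5 and ε = 1) unless enrolment rises to 144.

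The Bonferroni step within each outcome can stay as it is. Holm or the fixed order needs no change to recruitment, treatment or assessments, but a rule chosen after the results are seen gives no protection.
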